## Abstract

**Background:**

Cancer-Related Fatigue (CRF) is one of the most prominent subjective symptoms that cancer patients encounter, in particular individuals with gastrointestinal tumors. This fatigue significantly impacts their quality of life, impairs adherence to treatment, and may ultimately reduce overall survival rates. Moxibustion has gradually gained recognition as a therapeutic intervention for CRF. However, clinical evidence supporting the efficacy of moxibustion remains limited.

**Methods:**

This investigation employs a randomized, controlled, single-blinded trial design. A 1:1 random allocation method will be implemented to assign 74 participants to either the moxibustion group or the placebo moxibustion group. All participants will undergo eight sessions over 4 weeks, with sessions occurring twice weekly and lasting for 30 minutes each. Assessments for follow-up will take place at week 8. The primary outcome will be the percentage of patients who show a decrease of at least three points on the Brief Fatigue Inventory (BFI) at week 4. Secondary outcomes will encompass changes in the BFI, Quality of Life Questionnaire-Core 30 (QLQ-C30), Generalized Anxiety Disorder Scale-7 (GAD-7). Meanwhile, Blood cell counts and serum T lymphocyte subsets (CD3+, CD4+, CD8+, CD4+/CD8+) will be measured as exploratory outcomes. In addition, adverse events will be screened and documented throughout the study. An analysis adhering to the intention-to-treat(ITT) principle will be executed.

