### Study design

2.1

The LongHua Hospital affiliated to Shanghai University of Traditional Chinese Medicine will host this randomized, single-blinded, placebo-moxibustion controlled study. 74 patients who satisfy the gastrointestinal CRF inclusion requirements will be divided 1:1 between the moxibustion and placebo moxibustion groups at random. The trial is structured to include a 4-week intervention segment followed by a subsequent 4-week post-intervention surveillance phase. This report was based on the Standard Protocol Items: Recommendations for Interventional Trials checklist (12). This protocol is version 1.0. **Figure 1** shows a flowchart outlining the specifics of the trial’s procedure. **Table 1** offers a timetable that includes baseline, interventions, and evaluations.

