**Figure 1 f1:**
[figure not shown]
Flowchart of the study. BFI: the Brief Fatigue Inventory; QLQ-C30: Quality of Life Questionnaire-Core 30; GAD-7: Generalized Anxiety Disorder Scale-7; Blood cell counts (including leukocytes, hemoglobin, platelets, and lymphocytes);Serum T lymphocyte subsets (including CD3+, CD4+, CD8+, CD4+/CD8+).

**Table 1 T1:** Schedule of baseline, interventions, and assessments.

Study period	Baseline	Intervention phase				Follow-up phase
Time point	Week-1- 0	Week 1	Week 2	Week 3	Week 4	Week 8
Enrollment	•					
Eligibility screen	•					
Informed consent	•					
Medical history collection	•					
Randomization	•					
Intervention						
Moxibustion		•	•	•	•	
Placebo moxibustion		•	•	•	•	
Primary outcome						
percentage of patients showing a decrease of at least three points on the BFI at week 4					•	
Secondary outcomes						
BFI	•	•	•	•	•	•
QLQ-C30	•				•	
GAD-7	•				•	
Exploratory outcomes						
Blood cell counts	•				•	
serum T lymphocyte subsets	•				•	
Adverse events		•	•	•	•	

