##### The changes in BFI scores

2.7.3.1

It will be evaluated at weeks 1,2,3,4, 8.

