#### Safety evaluation

2.7.5

Adverse events (AEs) linked with moxibustion are burns, allergic reactions, and blistering, along with potential worsening of pre-existing conditions due to the therapy. In the event of any AEs, it is imperative for the practitioner to promptly assess their severity and implement suitable interventions, such as removing the heat source or consulting a dermatologist for severe burns. Any AEs noticed during the study need to be documented in the “Adverse Event Form”. It is imperative that both the management protocols and the resultant outcomes of these AEs are dutifully recorded with precision. In the event that a participant experiences serious AEs during treatment, the clinical trial shall be assessed and potentially terminated at the discretion of the researchers. Treatment termination details, including final time and outcome, will be documented for statistical analysis of AEs.

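### The abstract promises adverse-event screening for the whole study, but Table 1 schedules it only for weeks 1–4 and leaves the existing week-8 contact blank

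*Protocol article*

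**What the plan says.** Three places in the protocol article bear on when adverse events are collected.

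- **Abstract, Methods.** "adverse events will be screened and documented throughout the study". The same paragraph adds: "Assessments for follow-up will take place at week 8".
- **Section 2.7.5, Safety evaluation.** "Any AEs noticed during the study need to be documented in the “Adverse Event Form". No end date is given. The section lists burns, allergic reactions and blistering, "along with potential worsening of pre-existing conditions due to the therapy", and it requires the management and the outcome of each event to be recorded.
- **Table 1.** The columns after baseline are "Week 1 Week 2 Week 3 Week 4 Week 8". The row "Adverse events" has a mark at each of weeks 1 to 4 and none at week 8.

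Two other sections fix the length of the study and the existence of a late contact. Section 2.1 describes a "4-week intervention segment followed by a subsequent 4-week post-intervention surveillance phase". Section 2.7.3.1 says of the BFI: "It will be evaluated at weeks 1,2,3,4, 8". Table 1 agrees, with a BFI mark in the week-8 column.

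**The concern.** Staff work from the schedule of assessments. If they follow Table 1, nobody is asked about adverse events after week 4, even though the abstract tells readers that screening runs through the whole study. The second half of follow-up is called a surveillance phase, yet it contains no scheduled safety assessment.

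This matters because safety is named beside efficacy as an aim in the abstract, at the end of the Introduction and in the Discussion. Some of the event types in section 2.7.5 need not show themselves during a session; worsening of a pre-existing condition is the clearest example. Events from the final sessions may also still be open at the week-4 assessment. If nobody asks at week 8, what reaches the form from weeks 5–8 depends on what patients mention or staff happen to notice. A safety summary described as covering the study would then combine four weeks of scheduled assessment with four weeks of incidental reporting.

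**Working it through.** The article gives no figure of its own on this point, so there is nothing to reproduce. The check compares the text with the table and then does one piece of arithmetic.

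**1. Is the blank cell real, or a fault in reading the table?** The time-point header has seven fields: the label, baseline, weeks 1, 2, 3 and 4, and week 8. The adverse-event row also has seven fields. Aligned, they read:

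| | Baseline | Wk 1 | Wk 2 | Wk 3 | Wk 4 | Wk 8 |
|---|---|---|---|---|---|---|
| Adverse events | – | • | • | • | • | – |
| BFI | • | • | • | • | • | • |

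The BFI row carries a week-8 mark, so that column was read correctly. The empty adverse-event cell is very unlikely to be an extraction fault.

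**2. How long is the study?** From section 2.1: 4 weeks of intervention + 4 weeks of surveillance = 8 post-baseline weeks.

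**3. What share has no scheduled assessment?** Marks run to week 4, so the share is (8 − 4) / 8 = 4/8 = 50%. With a mark at week 8, the schedule would span 8 of 8 weeks.

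**4. Can the texts be read together?**

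| Source | Window for adverse events |
|---|---|
| Abstract, Methods | Whole study, with screening |
| Section 2.7.5 | During the study, events that are noticed; no end date |
| Table 1 | Weeks 1–4 |

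Sections 2.7.5 and Table 1 could coexist if the table showed active assessment and 2.7.5 covered passive reporting afterwards. That reading does not rescue the abstract, which promises screening as well as documentation throughout. No section limits collection to the treatment phase or explains the blank cell.

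**5. Does anything else change?** The primary outcome is read at week 4, and the sample size in section 2.9 rests on response proportions at week 4. Neither depends on the adverse-event schedule.

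**The case against.** The strongest case on the other side has four parts.

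*Later events are not shut out.* A reader might infer from Table 1 that no safety data at all are planned after week 4. The documents do not support that. Section 2.7.5 requires any event noticed during the study to be documented, without a week-4 cut-off, and section 2.6.3 requires medical events that may affect fatigue or immune status to be documented during the study period. This part stands: the gap is in scheduled assessment, not in every route of capture.

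*Outcomes of late events are already covered.* A reader might also infer that the outcome of a burn from the last session would go unrecorded. Section 2.7.5 asks for outcomes to be recorded and sets no time limit, so that is not established either. What can be said is that Table 1 offers no later point at which to do it.

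*Most expected events occur during sessions.* All eight sessions fall in weeks 1–4, and burns, blistering and allergic reactions would mostly appear then. Confining scheduled checks to the treatment phase is a defensible design. This limits the likely consequence, but it is not the design that the abstract describes, and section 2.7.5 also lists worsening of existing conditions.

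*An article leaves elicitation to the full protocol.* The method of asking at each visit may indeed be set out elsewhere, and its absence here is no fault. The point does not rest on missing detail; it rests on two statements in the same article that disagree.

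**Conclusion.** The point holds as an inconsistency with a practical consequence. The abstract's promise of study-wide screening, supported by the open-ended wording of section 2.7.5, conflicts with a schedule that stops at week 4 although a contact takes place at week 8. Four of the eight post-baseline weeks (50%) have no scheduled adverse-event assessment and rely on passive capture. Events that start or worsen after the last session may therefore be under-ascertained.

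How many would be missed cannot be estimated, because the article gives no rate of late events. The conclusion assumes that Table 1 is the schedule staff will follow and that the full protocol, which is not shown, does not already schedule an adverse-event assessment at week 8. The week-4 primary endpoint, the sample size and the power are unaffected. The matter is worth correcting because safety is a stated aim and the change is small, but it does not threaten the main efficacy result.

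**What to change.** Preferred:

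- Add an adverse-event mark in the week-8 column of Table 1.
- At that contact, ask about events since week 4 in the same way in both arms.
- Record the status of every event still open at week 4.
- State in section 2.7.5 that collection runs from the first session to week 8.

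Alternative: if scheduled collection is meant to end with treatment, say so in the abstract and in section 2.7.5, and limit the safety conclusion to the 4-week treatment phase.

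The preferred route costs one table cell, one sentence and a short enquiry at a contact that already exists. It needs no additional visit and no change to the sample size or the efficacy analyses. It should be done before patients reach week 8, since events not asked about then are hard to recover reliably later.

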**Discussion:**

This research aims to evaluate the efficacy and safety of moxibustion in patients with gastrointestinal CRF. Additionally, the study seeks to investigate the effects of moxibustion on the immune response in individuals diagnosed with gastrointestinal CRF.

## Introduction

1

The International Agency for Research on Cancer (IARC) reported in the ‘Global Cancer Statistics 2020’ that colorectal and gastric cancers are the third and fifth most frequently diagnosed malignancies globally (1). The advancement of diagnostic and therapeutic technologies has led to an increase in overall survival rates for individuals with gastrointestinal cancers. However, a troubling reality remains: studies suggest that a substantial proportion of patients between 52% to 90% either undergoing treatment or existing as survivors, endure an unyielding level of fatigue that resists conventional rest, a condition known as CRF (2). CRF has emerged as a pervasive and deeply felt symptom among cancer patients. A sweeping meta-analysis, amalgamating data from 129 studies and encompassing 71,568 cancer patients, has unveiled disparities in fatigue prevalence across various cancer subtypes. Most notably, gastrointestinal cancer patients report the most severe fatigue levels, hitting a high of 50%, which is considerably higher than those observed in gynecological (26.2%) and prostate (26.3%) cancer patients (3).

The 2023 second edition of the National Comprehensive Cancer Network (NCCN) guidelines defines CRF as a persistent, debilitating, and subjective experience of physical, emotional, and cognitive fatigue linked to the presence of cancer or its therapeutic interventions. This type of fatigue is disproportionate to recent activity levels and disrupts daily functioning (4). It is a more profound and enduring condition than the fatigue that follows physical exertion and is not alleviated through rest or sleep. CRF can have a profound impact on the physiological, psychological, and socioeconomic well-being of both patients and their primary caregivers, potentially diminishing quality of life, hindering treatment adherence, and impacting overall patient survival (5–7). Consequently, alongside treating the primary gastrointestinal cancer, attention must also be given to the management of fatigue symptoms and the enhancement of life quality for these patients.

Currently, there is a lack of widely accepted and efficacious pharmaceutical treatments for CRF. The NCCN endorses a range of non-pharmacological strategies, including exercise-based therapies, cognitive-behavioral interventions, sleep hygiene practices, and psychological support, which have shown potential in alleviating CRF (8), although their benefits may vary. With a significant number of patients experiencing CRF, there is a growing interest in complementary and alternative medicine (CAM) options (9). Moxibustion, a traditional CAM therapy involving the application of heat from burning herbs like mugwort to specific acupoints on the body. This treatment modality operates through direct or indirect thermal stimulation across a range of temperatures (10, 11). Moxibustion, appreciated for its straightforward application, non-invasive approach, and significant healing properties, has been employed in China for the management of CRF. Nevertheless, there is a lack of high-quality clinical trials to support the therapeutic benefits of moxibustion for CRF. The field is calling for rigorous, methodologically sound randomized controlled trials to ascertain the efficacy of moxibustion in treating CRF.

In response to these needs, we have crafted a randomized controlled trial aimed at assessing the efficacy and safety of moxibustion in treating gastrointestinal CRF and at exploring its potential effects on the immune function of patients afflicted with this condition.

## Methods

2

### Study design

2.1

The LongHua Hospital affiliated to Shanghai University of Traditional Chinese Medicine will host this randomized, single-blinded, placebo-moxibustion controlled study. 74 patients who satisfy the gastrointestinal CRF inclusion requirements will be divided 1:1 between the moxibustion and placebo moxibustion groups at random. The trial is structured to include a 4-week intervention segment followed by a subsequent 4-week post-intervention surveillance phase. This report was based on the Standard Protocol Items: Recommendations for Interventional Trials checklist (12). This protocol is version 1.0. **Figure 1** shows a flowchart outlining the specifics of the trial’s procedure. **Table 1** offers a timetable that includes baseline, interventions, and evaluations.

**Figure 1 f1:**
[figure not shown]
Flowchart of the study. BFI: the Brief Fatigue Inventory; QLQ-C30: Quality of Life Questionnaire-Core 30; GAD-7: Generalized Anxiety Disorder Scale-7; Blood cell counts (including leukocytes, hemoglobin, platelets, and lymphocytes);Serum T lymphocyte subsets (including CD3+, CD4+, CD8+, CD4+/CD8+).

**Table 1 T1:** Schedule of baseline, interventions, and assessments.

Study period	Baseline	Intervention phase				Follow-up phase
Time point	Week-1- 0	Week 1	Week 2	Week 3	Week 4	Week 8
Enrollment	•					
Eligibility screen	•					
Informed consent	•					
Medical history collection	•					
Randomization	•					
Intervention						
Moxibustion		•	•	•	•	
Placebo moxibustion		•	•	•	•	
Primary outcome						
percentage of patients showing a decrease of at least three points on the BFI at week 4					•	
Secondary outcomes						
BFI	•	•	•	•	•	•
QLQ-C30	•				•	
GAD-7	•				•	
Exploratory outcomes						
Blood cell counts	•				•	
serum T lymphocyte subsets	•				•	
Adverse events		•	•	•	•	

### Patient recruitment

2.2

The cancer wards and outpatient clinics of LongHua Hospital affiliated to Shanghai University of Traditional Chinese Medicine will be the source of gastrointestinal CRF patients. Posters and announcements will be posted on official platforms at the same time. For a preliminary screening, those who are interested might call the researcher at the number listed on the website. An impartial researcher will conduct an initial evaluation and in-person interview with those who first meet the requirements. After signing an informed consent form, those who fulfill the inclusion requirements will be assigned at random to either the moxibustion or placebo moxibustion groups. Personal data will be used solely for medical research, and each participant will have the freedom to leave the trial at any time.

### Eligibility criteria

2.3

#### Inclusion criteria

2.3.1

Prior to providing written informed consent for study participation, subjects must meet all of the following diagnostic criteria:Diagnosis of colorectal and gastric cancer according to the 2022 Chinese Clinical Society of Oncology’s (CSCO) guidelines.The tumor node metastasis (TNM) stage II or III based on the 8th edition of the American Joint Committee on Cancer (AJCC) Staging Manual.Fulfill the CRF diagnostic criteria outlined in the International Classification of Diseases (ICD-10).CRF occurred after the diagnosis of colorectal and gastric cancer and is linked to the cancer or its treatment.No gender restriction, age 18-70.The performance status of the Eastern Cooperative Oncology Group (ECOG) ≤ 2.BFI≥4.Prediction of survival ≤ 6 months.No previous Acupuncture or moxibustion treatment within the least 3 months.Possess normal cognitive function, capable of comprehending scale instructions and completing the assessment.Participation and signed informed consent are required.

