#### Exclusion criteria

2.3.2

Presence of serious diseases affecting the heart, liver, kidneys, or other major organs.Patients scheduled to undergo surgery, radiotherapy, or chemotherapy during the trial period.Pregnant or lactating women.Presence of intestinal perforation, hemorrhage, obstruction, or any other contraindications to moxibustion.Individuals with psychiatric conditions or substance abuse (drugs, alcohol, medications) compromising communication.Patients with ulcers, sores, or localized skin infections at the proposed moxibustion sites.Patients with respiratory diseases, a known allergy to moxibustion, or any other conditions for which moxibustion therapy is contraindicated.

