### Sample size calculation

2.9

Based on the preliminary research results, it was observed that 40% of patients in the moxibustion group and 10% in the placebo group exhibited a decrease of at least 3 points on the BFI at week 4. Calculations indicate that the sample size of 58 patients would ensure a study power of at least 80%, with a two-sided significance level of 0.05. To adjust for an anticipated dropout rate of 20%, 37 patients will be finally taken from for each group.

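### The mandatory survival criterion, as printed, admits only patients expected to live 6 months or less, which conflicts with the stage II–III, ECOG ≤ 2 population defined beside it

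*Protocol article*

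**What the plan says.** Section 2.3.1 (Inclusion criteria) states that "subjects must meet all of the following diagnostic criteria". One item is "Prediction of survival ≤ 6 months". The same list contains "The tumor node metastasis (TNM) stage II or III" and "The performance status of the Eastern Cooperative Oncology Group (ECOG) ≤ 2", an age range of 18 to 70, and a BFI of at least 4.

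Section 2.3.2 (Exclusion criteria) removes "Presence of serious diseases affecting the heart, liver, kidneys, or other major organs" and also "Patients scheduled to undergo surgery, radiotherapy, or chemotherapy during the trial period".

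Section 2.1 (Study design) sets a "4-week intervention segment followed by a subsequent 4-week post-intervention surveillance phase", so each patient is followed for 8 weeks. Section 2.7.2 places the primary outcome, a BFI response, at week 4. Section 2.9 allows 20% for dropout, and section 2.10 fills missing values with the last available evaluation.

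**The concern.** The survival item is a ceiling placed in a list where every item is compulsory. Taken literally, a stage II or III patient expected to live longer than 6 months is ineligible, however well the patient fits the other criteria. A patient expected to live only a few weeks passes this item, because it sets no floor.

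The other criteria describe non-metastatic disease, reasonable performance status and no serious organ disease. Section 2.7.3.2 refers to cancer survivors when it describes the quality-of-life instrument, and the Discussion cites a recommendation for survivors who have completed treatment. No section mentions palliative or end-of-life care, gives a reason for an upper limit on prognosis, or restates the limit.

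This is more than a typographical matter because the criterion decides who is randomised. If it is applied as printed, the trial recruits few patients or a different population. If screening staff silently apply something else, every enrolled patient with a longer prognosis departs from the published criterion, and section 2.8 requires deviations to be recorded and reported to the Ethics Committee. In both cases a reader cannot tell to whom the result applies.

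**Working it through.** **1. Is it a text-reading fault?** Unlikely. Two other thresholds in the same list, ECOG ≤ 2 and BFI ≥ 4, use both inequality signs and both make sense as printed.

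**2. The criteria side by side.**

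| Item | Section | Points towards |
|---|---|---|
| Predicted survival at most 6 months (compulsory) | 2.3.1 | very short prognosis only |
| TNM stage II or III (compulsory) | 2.3.1 | stage IV not admitted |
| ECOG ≤ 2 (compulsory) | 2.3.1 | preserved function |
| Serious major-organ disease excluded | 2.3.2 | removes an obvious reason for a short prognosis |
| Perforation, hemorrhage or obstruction excluded | 2.3.2 | removes further acute reasons |

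The first row pulls against the other four. The article gives no prognosis by stage, so how few patients would meet all five is a matter of clinical judgement.

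**3. The plan's own sample size.** Inputs from section 2.9: response 40% against 10%, two-sided 0.05, 80% power, 20% dropout. With the unpooled two-proportion formula:

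n = (1.960 + 0.842)² × (0.4 × 0.6 + 0.1 × 0.9) / 0.3² = 28.78, so 29 per group and 58 in total.

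29 / 0.8 = 36.25, so 37 per group and 74 in total. The stated figures reproduce. The allowance is 37 − 29 = 8 patients per group for losses of every kind.

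**4. What early deaths could do to that allowance (illustration).** The documents give no survival data. Assume exponential survival with median m weeks, so the proportion dead by week t is 1 − 0.5^(t/m).

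| Assumed median | Dead by week 4 | Dead by week 8 |
|---|---|---|
| 6 months (26 weeks) | 1 − 0.5^(4/26) = 10.1% | 1 − 0.5^(8/26) = 19.2% |
| 3 months (13 weeks) | 1 − 0.5^(4/13) = 19.2% | 1 − 0.5^(8/13) = 34.7% |

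Of 37 per group, this is 3.7 and 7.1 patients by week 4, and 7.1 and 12.8 by week 8. At the primary time point, deaths would take about half (10.1/20) to nearly all (19.2/20) of the allowance before any other dropout. Under section 2.10, the last BFI score of a patient who died would be carried forward.

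**The case against.** Four stronger readings are tempting, and the documents do not support them.

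- **That the sign is reversed, and that the intended rule is known.** A reader might infer that at least 6 months was meant. No section states the intended direction or any other cut-off. An item misplaced from the exclusion list would explain the text equally well.
- **That the criterion contradicts the 8-week follow-up.** It does not. Eight weeks is shorter than 6 months, and a patient with a 6-month prognosis can be followed for 8 weeks. The conflict is with stage, performance status and the organ-disease exclusion.
- **That deaths alone would exhaust the dropout allowance.** Only one of the four illustrative figures exceeds 20% (3-month median, week 8). Neither week-4 figure does, and week 4 is the time point for which the trial is sized.
- **That excluding planned surgery, radiotherapy or chemotherapy signals a good prognosis.** Patients near the end of life may also have none planned. Section 2.6.3 gives another reason for this exclusion: limiting confounding of the fatigue and immune outcomes.

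It is also fair to say that the article condenses a fuller protocol, and that sites may be working from a correct criterion. This makes the consequences for enrolment conditional on what was applied. It does not excuse the printed text, because the point is an explicit criterion that conflicts with its neighbours, not a detail left out for brevity.

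**Conclusion.** The point holds as an internal inconsistency in a compulsory eligibility threshold, and it must be resolved. The printed criterion cannot sensibly stand beside stage II–III disease, ECOG ≤ 2 and the exclusion of serious major-organ disease, and nothing elsewhere corrects or justifies it. Confidence is high that the text is wrong as printed, and lower about what was intended.

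The harm arises only if the printed rule was used at screening. Recruitment would then probably be very small or drawn from a population outside the rationale, and deaths could take a large share of the 20% allowance: about 10–19% by week 4 and 19–35% by week 8. Those ranges rest on exponential survival and assumed medians of 6 to 3 months. They show scale only, and the finding does not depend on them.

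**What to change.** The sponsor should compare the survival criterion with the ethics-approved protocol and the screening form, and reconcile it with the other items in sections 2.3.1 and 2.3.2. The published criterion should then be corrected to the approved one; this review proposes no replacement cut-off. The sponsor should also confirm which rule was applied at screening and re-check patients already screened. If the approved protocol carries the same wording, the criterion needs an amendment as well as a correction to the article.

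The cost is a document check, a short correction or amendment notice, and a review of the screening records. The design and the sample size of 74 do not change, and no extra patients are needed.
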